## 9.0 Study Endpoints

### 9.1 Primary and secondary endpoints.

#### Primary endpoints:

Phase 1: Incidence of treatment-emergent adverse events and laboratory values over 8 weeks of treatment to known frequency of anakinra-related AEs in other populations.

Phase 2: Need for dose escalation as determined by within individual change over 8-week treatment period compared to change over 8-week observational period in the 2 most bothersome symptoms for each enrolled patient, selected from measures for the MDRI. Choices are below in bold. These 2 symptoms will be monitored by one or more of the assessments below. If the Minimal Clinically Important Difference (MCID) that is defined below is not achieved after 8 weeks of treatment, or there has been a decrease of more than the MCID between 8 and 16 weeks after an increase greater than MCID at week 8, the dose will be escalated (see Section 27.7). If the MCID is not achieved after 8 weeks on maximum trial dose of 200mg (max dose 8 mg/kg/day), treatment with anakinra may be discontinued (see Section 27.7).

- Sanfilippo **Behavior** Rating Scale (SBRS): MCID = 0.25 SD for each scale
  - Symptoms described in table below:

|                         |                                                                                                                                        |                           |
|-------------------------|----------------------------------------------------------------------------------------------------------------------------------------|---------------------------|
| Body Movements          | Makes large complex movements of their body, such as spinning, twirling or repeatedly bouncing up and down.                            | Movement                  |
| Object Interaction      | Examines or manipulates some novel or unfamiliar objects repeatedly.                                                                   |                           |
| Activity/Routines       | Never plays with one object or engages in one activity for very long.                                                                  |                           |
| Emotional Function      | Expresses emotions inappropriate to the situation.                                                                                     | Social/emotional function |

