| Sanfilippo Behavior Rating Scale                       |           | X                               | X                 |                                                              | X                                | X                                      |
| Non-communicating Children's Pain Checklist-Revised    |           | X                               | X                 |                                                              | X                                | X                                      |
| Parent reported outcomes (PROMIS) d         |           | X                               | X                 |                                                              | X                                | X                                      |
| Seizure - parent assessment x 1 week                   |           | X h                  | X                 |                                                              | X                                | X                                      |
| Movement - parent assessment x 1 week                  |           | X h                  | X                 |                                                              | X                                | X                                      |
| Individual Clinical Response                           |           | X                               | X                 |                                                              | X                                | X                                      |
| Gait assessment                                        |           | X                               | X                 |                                                              | X                                |                                        |
| Vineland-III                                           |           | X                               |                   |                                                              | X                                |                                        |
| Stair climb                                            |           | X                               | X                 |                                                              | X                                |                                        |

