| Sleep Diary – parent assessment x 1 week               |           | X h                  | X                 |                                                              | X                                | X                                      |
| Stooling Survey                                        |           | X                               | X                 |                                                              | X                                | X                                      |
| Safety labs (CBCD, BMP, LFT, lipid panel) i | X         | X                               | X                 | X                                                            | X                                | X                                      |
| Thyroid studies                                        | X         |                                 |                   |                                                              |                                  |                                        |
| Blood biomarkers                                       |           | X                               | X                 |                                                              | X                                | X                                      |
| Urine biomarkers                                       |           | X                               | X                 |                                                              | X                                | X                                      |
| Stool collection                                       |           | X                               | X                 |                                                              | X                                | X                                      |
| Genetic biomarkers (optional)                          |           | X                               | X                 |                                                              | X                                | X l                         |
| CSF collection (optional)                              |           | X                               | X                 |                                                              | X                                | X (week 44 only)                       |

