f After written informed consent but before study treatment initiation, only SAEs associated with protocol-imposed interventions will be recorded. After study drug initiation, all AEs, SAEs, and pregnancy will be recorded until week 44 or the Early Termination visit. If a subject is discontinued from the study prematurely, AEs and SAEs will be recorded at the Early Termination visit.

g During these contacts, study staff will ask about dose administration and seek information on AEs and SAEs by specific questioning. Information on all AEs and SAEs should be recorded in the subject's medical record and on the AE eCRF.

h Diaries will be completed at week -6 to avoid the potential impact of travel on these outcomes.

i Plasma and serum samples collected and stored for PK and anti-drug antibody studies.

j Buffy coat will only be collected on Week -8, Day 1, and Week +36.

k Week +24 safety labs only if dose was increased at week +16.

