### **10.4 Laboratory Evaluations**

Blood and urine will be collected at the time points described in the Schedule of Events.

Complete blood count with differential (CBCD), liver function tests (LFTs), lipid panel, and basic metabolic panel (BMP) will be performed at Quest Diagnostics or LabCorp at Screening, Week -8, Day 1, Week +2, Week +4, Week +8, Week +12, Week +16, Week +20, Week +24 (only if dose increased at week +16), Week +36, and Week +44. Thyroid function tests (TSH, Free T4) and Quantiferon-TB Gold test will be obtained at Screening.

Anti-anakinra antibodies will not be measured during this pilot study; the rationale for this is based on prior studies showing no effect of anti-anakinra antibodies on pharmacokinetic (PK) parameters, efficacy outcomes or adverse events (AEs) and low incidence of neutralizing anti-anakinra antibodies. However, serum will be collected at Day 1, Week +8, Week +36, and Week +44 and stored for possible future testing of anti-anakinra antibodies if needed for interpretation of safety or efficacy results.

Plasma will be collected and stored for future PK studies at Day 1, Week +8, Week +36, and Week +44.

For post-menarche female patients, a urine pregnancy test will be performed at Screening and at each study visit.

Plasma, serum, urine, and PAXgene tube for RNA will be collected for future biomarker studies at Week -8, Day 1, Week +8, Week +16, Week +36, and Week +44. Consent will be requested to perform these additional biomarker studies on

stored samples in the future as well as genome wide association studies (GWAS) and/or large-scale genomics/transcriptomics assays such as sequencing, methylation and expression.

Buffy coat for DNA will be collected for future biomarker studies at Week -8, Day 1, and Week +36.

Stool will be collected at Week -8, Day 1, Week +8, Week +16, Week +36, and Week +44 for future microbiome studies.

Whole blood will be collected at Week -8, Day 1, Week +8, Week +16, Week +36 and Week +44.

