### **27.7 Dosing**

In this study anakinra subcutaneous (SC) will be administered at a dose level of 100 mg SC once daily. Anakinra will be administered every other day in patients who have severe renal insufficiency or end stage renal disease (defined as creatinine clearance < 30 mL/min as estimated from serum creatinine levels).

**Dose will be increased to 200 mg SC once daily**, with a maximum dose limit of 8 mg/kg/day, at **Week +8** if the change in at least one of the two most bothersome outcomes selected by the parents/guardians at the Day 1 visit has not improved by  $\geq$  the MCID as defined in Section 9.1. If the MCID is not achieved after 8 weeks on maximum trial dose of 200mg (max dose 8 mg/kg/day), **treatment with anakinra may be discontinued after a review and discussion between the study PI and subject's parent(s) of their child's individual results from all study outcome measures.**

**Dose will be increased to 200 mg SC once daily**, with a maximum dose limit of 8 mg/kg/day, at **Week +16** if the change in at least one of the two most bothersome outcomes selected by the parents/guardians at the Day +1 visit have worsened by  $\geq$  the MCID as defined in Section 9.1 between week +8 and week +16, after an improvement from Day +1 to week +8. If the MCID is not achieved after 8 weeks on maximum trial dose of 200mg (max dose 8 mg/kg/day), **treatment with anakinra may be discontinued after a review and discussion between the study PI and subject's parent(s) of their child's individual results from all study outcome measures.**

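### For subjects escalated at Week +16, the MCID check after 8 weeks on 200 mg falls at Week +24, where no outcome measure is scheduled

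*Protocol*

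**What the plan says.** Section 27.7 of the protocol allows escalation to 200 mg daily at Week +8 (insufficient improvement) or at Week +16 (worsening after an earlier improvement). Each paragraph ends with the same provision: "If the MCID is not achieved after 8 weeks on maximum trial dose of 200mg (max dose 8 mg/kg/day"), treatment may be stopped after the principal investigator and parents have discussed "their child's individual results from all study outcome measures". Section 9.1 carries the rule in the Phase 2 primary endpoint: "treatment with anakinra may be discontinued (see Section 27.7").

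The Schedule of Events in section 10.2 places Week +24 in a column with Weeks +2, +4, +12 and +20. The only row marked in that column is "Safety labs (CBCD, BMP, LFT, lipid panel"). Footnote k reads "Week +24 safety labs only if dose was increased at week +16", and section 10.4 lists "Week +24 (only if dose increased at week +16") among the safety-lab times. The CSHQ, SBRS, NCCPC-R, APSI, PROMIS Fatigue and the one-week movement log are scheduled at Week -8 (diaries at Week -6), Day +1 and Weeks +8, +16, +36 and +44.

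**The concern.** The condition for the review is a matter of fact: whether the MCID was reached after 8 weeks at the higher dose. It needs a score taken at that time. If none is scheduled, the investigator and parents have only the Week +16 results, obtained before any 200 mg dose, and these say nothing about response to that dose. The protocol itself treats 8 weeks without an MCID gain as a reason to reconsider daily injections. For one of its two escalation routes it does not collect what is needed to apply that judgement.

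A statistical analysis plan could not repair this. It cannot supply a questionnaire that the visit schedule never collects, and the dosing rule belongs to the protocol.

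**Working it through.** No sample size, power or error-rate figure is involved. The check is timeline arithmetic against the Schedule of Events.

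**Inputs**
- Escalation weeks: +8 and +16 (section 27.7).
- Time on 200 mg before the check: 8 weeks (sections 27.7 and 9.1).
- On-treatment weeks with MCID scales after Day +1: +8, +16 and +36 (section 10.2).
- End of treatment: Week +36 (section 10.1).
- Visit windows: ±2 days for the Week +24 column, ±1 week for Weeks +16 and +36 (section 10.2).

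**Check week = escalation week + 8**
- Week +8 route: 8 + 8 = 16. All MCID scales and the movement log are marked at Week +16, so the rule can be applied. Week +16 is still not a full outcome visit: the row "Gait assessment" is blank in that column, as are stair climb and Vineland. None of these three has an MCID.
- Week +16 route: 16 + 8 = 24. Only safety labs are marked, so the rule cannot be applied.

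**Next available score for the Week +16 route**
- Nominal: 36 − 16 = 20 weeks after escalation, with 36 − 36 = 0 weeks of treatment left.
- Using the windows to shorten the gap (Week +16 visit a week late, Week +36 visit a week early): 35 − 17 = 18 weeks. The windows do not close it.

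**Other contacts that might supply a score**
- Contacts every 4 weeks. Footnote g limits their content: "During these contacts, study staff will ask about dose administration and seek information on AEs and SAEs by specific questioning". No scale is administered.
- Unscheduled visits (section 10.20) are with local physicians, for concerning signs or symptoms.
- The early termination visit (footnote a) repeats the Week +44 procedures, including the scales, but it follows discontinuation and cannot inform it.

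**Reference visit for the MCID on 200 mg.** Section 27.7 does not say which earlier visit the 200 mg score is compared with. Two constructed examples, in MCID units on one outcome, show that this matters on both routes:
- Week +16 route: a gain of 3 by Week +8, then a loss of 1 by Week +16, can trigger escalation. The subject is still 3 − 1 = 2 above Day +1. Against Day +1 the MCID is already met before any 200 mg dose; against Week +16 it is not.
- Week +8 route: a loss of 1 by Week +8, then a gain of 1 by Week +16, gives −1 + 1 = 0 against Day +1 (not met) but +1 against Week +8 (met).

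**The case against.** The strongest reply is that little depends on this check. Missing the MCID never forces a stop, because 27.7 leaves the decision to a discussion. Section 13.0 (item 6) and section 14.0 let a subject stop at any time for any reason, and subjects who stop the drug are asked to remain in follow-up. The 4-weekly contacts give families an occasion to say that the higher dose is not helping. This is also a 20-subject open-label pilot. All of this stands, and it limits the consequence. It does not answer the mismatch: discretion covers what to do once the MCID is known to be missed, and for this route that cannot be known when the rule calls for it.

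A reader might infer that children who gain nothing from 200 mg are bound to stay on injections until Week +36. The documents do not support that, for the reasons just given.

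A reader might also infer that a large share of the cohort is affected. The protocol gives no test-retest correlation, treatment effect or correlation between outcomes from which to calculate a share. The wording of the triggers also varies: the operative text of 27.7 refers to at least one of the two outcomes, while the worked examples speak of the chosen items and of both outcomes. Any percentage would rest on assumed inputs and on a choice of reading.

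**Conclusion.** The point holds and is wrong as written: for Week +16 escalators, 27.7 and 9.1 set a check that the schedule cannot serve. The firm figure is the delay. The first score on 200 mg comes nominally 20 weeks after escalation instead of 8, at the end of treatment. This rests only on the protocol's own visit weeks. The schedule column, footnote k and section 10.4 agree with one another, so a misread table does not explain it.

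The consequence is limited to losing the score that should inform a discretionary review, in a subgroup whose size the protocol does not determine. The primary endpoint is unaffected, because the escalation decisions at Weeks +8 and +16 both have scores. The Day 0 to Week +36 change is still measured, and safety labs and adverse-event contacts continue. A reader might infer that the 8-week secondary comparison is lost for these subjects. That depends on how section 9.1's phrase about the maximum effective and tolerated dose is read, and the protocol does not settle it.

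The unstated reference visit is a related drafting gap. It applies equally to both routes, since the same sentence closes each paragraph.

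**What to change.** 1. Under the existing footnote k condition (dose increased at Week +16), add to Week +24 the caregiver-reported measures for the two chosen symptoms, preferably all MDRI forms. Send them remotely, with the one-week movement log where movement was chosen. The check then falls 24 − 16 = 8 weeks after escalation, with 36 − 24 = 12 weeks of treatment left to act on it.
2. State in 27.7, for both escalation routes, the reference visit against which the MCID on 200 mg is judged.
3. If the investigators do not want the extra assessment, state instead that Week +16 escalators have no 8-week MCID review and continue to Week +36 unless stopped for another reason.

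The cost is one conditional schedule entry, a short addition to 27.7 and a small extra caregiver burden for Week +16 escalators only. No additional site visit is needed: these subjects already have Week +24 labs, which section 10.26 allows to be drawn at home or at a local laboratory.

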**For example:**

- At week +8, if a subject has not improved in the chosen items then the dose will be increased to 200 mg SC daily.
- At week +8, if a subject has improved, then the dose stays at 100 mg SC daily. However, if this individual then has worsening of the two most bothersome outcomes from week +8 to week +16, after improving from day 1 to week +8, the dose will be increased to 200 mg SC daily at that point (i.e. increase at week +16 after not increasing at week +8).

**Dose will be decreased by 50 mg SC once daily** at any time throughout the study if a participant develops any of the following:

- Neutropenia  $<1200$  cells/microliter persistent for  $\geq 2$  weeks
- Thrombocytopenia  $<50 \times 10^9$  platelets/liter persistent for  $\geq 2$  weeks
- Mild/moderate hypersensitivity reactions including urticaria, rash, and pruritis
- Participants develops a CTCAE grade 3 AE

**Anakinra will be stopped** if the AE above does not resolve within 2 weeks of decreasing the dose by 50 mg SC once daily. Anakinra will be restarted at 0.5 times the last dose administered once the AE is resolved. If the AE recurs with restarting anakinra, it will be discontinued and the subject monitored per protocol.

The starting dose is the same dose level as recommended for adult rheumatoid arthritis patients. The dose escalation is within the range of the recommended dose in Neonatal onset multisystem inflammatory disease (NOMID), including also pediatric patients, is related to body-weight, with a recommended starting dose of 1-2 mg/kg up to a maximum dose of 8 mg/kg.

Smaller children with lower body weight need higher dose levels/kg body-weight in order to achieve similar anakinra serum exposure as in older, heavier children, due to a higher capacity to eliminate anakinra/kg body-weight, based on pharmacokinetic data in 22

systemic-onset juvenile idiopathic arthritis (SJIA) pediatric patients in the age range 2-17 years.

As an example, based on this study, a patient with a body-weight of 20 kg is predicted to require a dose of 4 mg/kg/day to achieve similar anakinra exposure (area under the curve [AUC]0-24h, ss and Cmin, ss) as a dose of 100 mg in a 50 kg patient. Additional examples are given below:

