## 4.0 Background

Sanfilippo syndrome, or mucopolysaccharidosis type III (MPS III), is a genetic disorder of metabolism, associated with insufficient production of a lysosomal enzyme crucial for degradation of heparan sulfate. As a consequence, buildup of heparan sulfate causes progressive, irreversible neurodegeneration. There are four variants of MPS III, distinguished by the lysosomal enzyme deficiency: Heparan-N-sulfatase (MPS IIIA),  $\alpha$ -N-Acetylglucosaminidase (MPS IIIB), AcetylCoA:N-acetyltransferase (MPS IIIC) and N-Acetylglucosamine 6-sulfatase (MPS IIID). MPS IIIA and MPS IIIB are the most common subtypes.

Unlike other types of MPS which involve considerable somatic complications, the most significant aspect of MPS III is neurodegeneration which manifests in stages of developmental disruption and decline, defined by Cleary and Wraith. Their 3-stage model involves: 1) developmental delay in cognition and language before age 3-4 years, 2) temper tantrums, hyperactivity, aggression, sleep disorder, and a further loss of cognitive and language function from age 3-4 years to age 8-10 years, and 3) loss of motor function, feeding difficulties, and seizures from age 8-10 years. Recent work has determined that there is a loss of about 15 IQ points per year in children with MPS IIIA who are younger than 6 years and that they do not surpass a mental age equivalent of 30 months. The advancing disease causes the neurobehavioral profile to meet diagnostic criteria for autism^3, and to overlap with Kluver-Bucy syndrome. A study of patients with both MPS IIIA and IIIB in several European countries found comparable patterns of disease progression in the groups, with delayed language development and cognitive decline, as well as disruptive behavior, particularly in children diagnosed before age 5.

The neurobehavioral symptoms associated with MPS III are highly disruptive and distressing to families, have a significant impact on the quality of life for the patient and family, and likely interfere with adjunctive therapeutic attempts at supporting the child. However, despite the universal acknowledgment that these neurobehavioral symptoms are a prominent concern for MPS III, these symptoms have not been the therapeutic target.

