### ***13.2 Definitions for recording/reporting adverse events***

### *Adverse Event*

An AE is any symptom, sign, illness or experience that develops or worsens in severity during the course of the study. Intercurrent illnesses or injuries will be regarded as AEs. Abnormal results of laboratory or diagnostic procedures are considered to be AEs if the abnormality:

- ☐ Results in study withdrawal
- ☐ Is associated with a serious adverse event (SAE)
- ☐ Is associated with clinical signs or symptoms
- ☐ Leads to additional treatment or to further diagnostic tests
- ☐ Is considered by the Investigator to be of clinical significance

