### *Suspected Adverse Reaction*

A suspected adverse reaction is an AE for which there is a reasonable possibility that the drug caused the AE.

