### *Serious Adverse Event (SAE)*

An SAE is any AE that is:

- ☐ Fatal
- ☐ Life-threatening
- ☐ Requires or prolongs a hospital stay
- ☐ Results in persistent or significant disability or incapacity
- ☐ A congenital anomaly or birth defect

Important medical events are events that may not be immediately life-threatening, but are clearly of major clinical significance and may be SAEs. They may jeopardize the subject, and may require intervention to prevent one or the other serious outcomes noted above.

*Hospitalization*

Hospitalization shall include any initial admission (even if less than 24 hours) to a healthcare facility as a result of a precipitating clinical adverse effect; to include transfer within the hospital to an intensive care unit. Hospitalization or prolongation of hospitalization in the absence of a precipitating, clinical adverse effect (e.g. for a preexisting condition not associated with a new adverse effect or with a worsening of the preexisting condition; admission for a protocol-specified procedure) is not, in itself, a serious adverse effect.

*Expected Adverse Event*

Expected AEs are those that are known to be associated with or have the potential to arise as a consequence of participation in the study. This will include any AE or SAE that are expected consequences of having MPS . These expected events include but are not limited to, injection site reactions, injection site pain, headache, seizures, symptoms of movement disorder, sinusitis/ear infections, upper respiratory infection, fevers, nausea, vomiting, diarrhea, skin rash, pain, cardiac valve insufficiency, obstructive sleep apnea, kyphoscoliosis, genu valgum, cervical cord compression, hearing loss, in-toeing, osteonecrosis of the femoral head, retinitis pigmentosa with vision impairment, carpal tunnel syndrome, and trigger fingers.

*Unexpected Adverse Event*

An AE or suspected adverse reaction is considered unexpected if it is not listed in the drug package insert or Protocol at the specificity or severity that has been observed.

*Unanticipated Problems Involving Risk To Subjects or Others (UPIRTSO)*

An AE that in the opinion of the PI is unexpected, related to the drug, and serious.

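### The Grade 3 dose-reduction trigger in 27.7 also catches events clearly not caused by anakinra, and a fixed disease event would keep the child off drug

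*Protocol*

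**What the plan says.** Section 27.7 (Dosing) requires a 50 mg reduction of the daily dose, at any time in the study, on any of four triggers: persistent neutropenia, persistent thrombocytopenia, a mild or moderate hypersensitivity reaction, or, in the fourth item, "Participants develops a CTCAE grade 3 AE". The drug is then stopped "if the AE above does not resolve within 2 weeks of decreasing the dose by 50 mg SC once daily". On restart the rule is "Anakinra will be restarted at 0.5 times the last dose administered once the AE is resolved". If the event recurs after restart, the drug is discontinued. None of these steps leaves room for investigator judgement about cause.

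Section 13.2 defines adverse events regardless of cause: "Intercurrent illnesses or injuries will be regarded as AEs". Of expected events it says "This will include any AE or SAE that are expected consequences of having MPS", and its list includes "hearing loss, in-toeing, osteonecrosis of the femoral head, retinitis pigmentosa with vision impairment". The same section separately defines events with a possible drug cause: "A suspected adverse reaction is an AE for which there is a reasonable possibility that the drug caused the AE". Section 13.3 has every event classified as related or unrelated. The Grade 3 trigger uses neither distinction.

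**The concern.** Read together, 27.7 and 13.2 oblige the site to cut the dose for a Grade 3 fracture, an unrelated illness or a step in the natural course of MPS III, even when nobody thinks anakinra was responsible. The harder problem is the restart condition. The Background says that "buildup of heparan sulfate causes progressive, irreversible neurodegeneration". A fixed deficit that arises or worsens on treatment and reaches Grade 3 may never resolve, and the rule then gives no route back to drug. A child could lose most of the treatment period to an event that stopping anakinra cannot help. The trial would lose exposure in a cohort of 20 without any gain in safety.

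**Working it through.** The plan states no figure to reproduce. The inputs from the protocol are the 100 mg starting dose, the 200 mg escalated dose capped at 8 mg/kg/day, the 50 mg cut, the 2-week limit and the 0.5 restart factor (27.7); 36 weeks of treatment (10.1); 20 subjects (6.0); and the 85% dose threshold for the protocol-compliant population (12.1).

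**Dose path (cut, stop, restart).**
- On 100 mg: 100 − 50 = 50 mg, then 0, then 0.5 × 50 = 25 mg.
- On 200 mg (a child of at least 25 kg, since 8 × 25 = 200): 200 − 50 = 150 mg, then 0, then 0.5 × 150 = 75 mg.

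**Time off drug if the event never resolves.** With the cut at week w and the stop at w + 2, weeks without drug = 36 − (w + 2).

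| Cut at | Weeks off drug, of 36 |
|---|---|
| Week +4 | 36 − 6 = 30 |
| Week +12 | 36 − 14 = 22 |
| Week +20 | 36 − 22 = 14 |

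The full schedule is 36 × 7 = 252 daily doses, and 15% of that is 37.8. If planned doses means the full schedule, 38 missed days put a child below the 85% threshold. The shortest case in the table, 14 × 7 = 98 days, does so comfortably.

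**How many children.** The protocol gives no background Grade 3 rate. Let p be the assumed probability that a child has a clearly unrelated Grade 3 event within 36 weeks. Expected forced cuts are 20p. The chance of at least one is 1 − (1 − p)^20, taking children as independent. If events are spread evenly over treatment, the expected number before Week +8 is 20p × 8/36.

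| p (assumed) | Expected cuts of 20 | Chance of at least one | Expected before Week +8 |
|---|---|---|---|
| 1% | 0.2 | 18% | 0.04 |
| 2% | 0.4 | 33% | 0.09 |
| 5% | 1.0 | 64% | 0.22 |
| 10% | 2.0 | 88% | 0.44 |

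These are cuts. The share that would still be unresolved 2 weeks later, and so lead to a stop, is not known.

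**Does another section override the rule?** Section 14.0 replaces the cut with discontinuation for serious infection, malignancy, severe hypersensitivity and the liver criteria, so those events fall outside this point. Sections 13.3 and 13.4 and Appendix A contain no exemption from 27.7 for unrelated events. Appendix A exempts certain disease-related serious events only from expedited IRB reporting.

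**The case against.** The strongest defence is that an all-cause trigger is a deliberate, conservative choice. The neutropenia and thrombocytopenia triggers are bare laboratory limits, the infection and malignancy stops in 14.0 apply whatever the cause, and the Grade 3 and Grade 4 criteria in 13.4 carry no causality condition. This is an open-label, single-arm pilot with safety as its first objective and one independent Monitor reviewing every 6 months. Seizures and movement symptoms are both expected disease events and study outcomes, so drug-induced worsening could be put down to the disease. An objective severity trigger avoids that risk.

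Much of this stands. A reader might infer that the Grade 3 item is the only trigger without a causality condition. It is not. A reader might also see a conflict with 13.3, which lets follow-up of an event end at stabilization or once the treatment is ruled out as cause. That passage governs how long events are followed. It is not a dosing rule, so nothing is contradicted. Nor does Appendix A's expectation of many disease-related serious events show that the problem will be common, because it gives no rate, grade or duration. The harmful case is narrow: new or worsened on treatment, Grade 3, clearly unrelated, outside 14.0 and unresolved at 2 weeks. For events that do resolve, nothing in 27.7 bars a previously reduced child from the Week +8 escalation.

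The defence does not justify acting on events where there is no doubt about cause. The protocol gives no rationale for including them. Section 13.4 lists reasons for which the study may be terminated, which leaves room for review, whereas 27.7 acts automatically. The concern about misattribution is met by keeping the cut as the default.

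**Conclusion.** The point holds as a modest, inexpensive improvement to 27.7. As written, a Grade 3 event clearly unrelated to anakinra must cut the dose, and one that never resolves keeps the child off drug for the rest of treatment: 30, 22 or 14 of 36 weeks for a cut at Week +4, +12 or +20. Those durations are worst cases and assume that the event is permanent. The number of children affected is unknown and probably small.

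A reader might infer that the Phase 2 primary endpoint, need for dose escalation, is materially distorted because some children are judged at Week +8 on less than 100 mg. The numbers do not support this. Under assumed rates of 1% to 10%, the expected number of such children is 0.04 to 0.44 of 20, and drug-related cuts before Week +8, which are legitimate, have the same effect and would remain.

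**What to change.** Reword the fourth trigger in 27.7 to: *a CTCAE Grade 3 AE, unless clearly due to the underlying disease or another cause, with the reason documented*. State that the dose is cut whenever there is doubt. Leave the other three triggers, the discontinuation criteria in 14.0 and the stopping rules in 13.4 unchanged.

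The cost is one phrase in an amendment and one documented reason per exempted event. The downside is that attribution in an open-label single-arm trial is a judgement, which is why only clearly unrelated events are exempt. Events that could be either disease or drug, such as worsening seizures, would usually still trigger the cut. If they do not resolve, the stop would still follow.
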